## 8. 5 Reporting procedures

A special section is designated to adverse events in the case report form. The following details must thereby be entered:

- Type of adverse event
- Start (date and time)
- End (date and time)
- Severity (mild, moderate, severe)
- Serious (no / yes)
- Unexpected (no / yes)
- Outcome (resolved, ongoing, ongoing – improved, ongoing – worsening)
- Relation to study drug (unrelated, possibly related, definitely related)

Adverse events are to be documented in the case report form in accordance with the above mentioned criteria.

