**7.3.12. Benefit and risk assessment**

Benefits

- Reduction of HCV-replication and improvement of liver function with consecutive improvement of quality of life and reduced HCV-associated morbidity and mortality

Risks:

- Potential increase of serum creatinine after conversion, which however is anticipated to be reversible. In case of a significant decrease of graft function, defined as 50% reduction of the glomerular filtration rate (GFR) in subjects with a GFR ≥50 ml/min at baseline and as 30% reduction of the GFR in subjects with a GFR <50 ml/min at baseline, the study drug will be discontinued in the respective study participant and immunosuppression re-converted to a tacrolimus-based regimen.

In case of serious side effects or serious other medical safety concerns, single study participants will be withdrawn or the whole study prematurely terminated; the immunosuppression will be re-converted to a tacrolimus-based regimen.

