## 8. 2 Serious adverse events (SAEs)

A Serious Adverse Event (SAE) is defined by the International Conference on Harmonization (ICH) guidelines as any AE fulfilling at least one of the following criteria:

- results in deaths.
- Life-threatening – defined as an event in which the subject was, in the judgment of the investigator, at risk of death at the time of the event; it does not refer to an event that hypothetically might have caused death had it been more severe.
- Requiring subject's hospitalization or prolongation of existing hospitalization – inpatient hospitalization refers to any inpatient admission, regardless of length of stay.
- Resulting in persistent or significant disability or incapacity (i.e., a substantial disruption of a person’s ability to conduct normal life functions).
- Congenital anomaly or birth defect.
- Is medically significant or requires intervention to prevent at least one of the outcomes listed above.

Life-threatening refers to an event in which the subject was at risk of death at the time of the event. It does not refer to an event that hypothetically might have caused death if it were more severe.

Important medical events that may not immediately result in death, be life-threatening, or require hospitalization may be considered as SAEs when, based upon appropriate medical judgment, they may jeopardize the subject and may require medical or surgical intervention to prevent one of the outcomes listed in the definitions above.

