## 8. 3 Severity of adverse events

The severity of clinical AEs is graded on a three-point scale: mild, moderate, severe, and reported on specific AE pages of the CRF.

If the severity of an AE worsens during study drug administration, only the worst intensity should be reported on the AE page. If the AE lessens in intensity, no change in the severity is required.

If an AE occurs during a washout or placebo run-in phase and afterwards worsens during the treatment phase, a new AE page must be filled in with the intensity observed during study drug administration.

- **Mild**

Event may be noticeable to subject; does not influence daily activities; the AE resolves spontaneously or may require minimal therapeutic intervention;

- **Moderate**

Event may make subject uncomfortable; performance of daily activities may be influenced; intervention may be needed; the AE produces no sequelae.

- **Severe**

Event may cause noticeable discomfort; usually interferes with daily activities; subject may not be able to continue in the study; the AE produces sequelae, which require prolonged therapeutic intervention.

A mild, moderate or severe AE may or may not be serious. These terms are used to describe the intensity of a specific event (as in mild, moderate, or severe myocardial infarction). However, a severe event may be of relatively minor medical significance (such as severe headache) and is not necessarily serious. For example, nausea lasting several hours may be rated as severe, but may not be clinically serious. Fever of 39°C that is not considered severe may become serious if it prolongs hospital discharge by a day. Seriousness rather than severity serves as a guide for defining regulatory reporting obligations.

**8. 4** Relationship to study drug

For all AEs, the investigator will assess the causal relationship between the study drug and the AE using his/her clinical expertise and judgment according to the following algorithm that best fits the circumstances of the AE:

- Unrelated
  - May or may not follow a reasonable temporal sequence from administration of the study product
  - Is biologically implausible and does not follow known response pattern to the suspect study drug (if response pattern is previously known)
  - Can be explained by the known characteristics of the subject’s clinical state or other modes of therapy administered to the subject.
- Possible related
  - Follows a reasonable temporal sequence form administration of the study drug.

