### 8. 5. 1 Reporting procedures for SAEs

In the event of serious, the investigator has to use all supportive measures for best patient treatment. A written report is also to be prepared and made available to the clinical investigator immediately.. The following details should at least be available:

- Patient initials and number
- Patient: date of birth, sex, ethical origin
- The suspected investigational medical product (IMP)
- The adverse event assessed as serious
- Short description of the event and outcome
- If applicable, the initial report should be followed by the Follow up report, indicating the outcome of the SAE.

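### The mandatory adverse-event outcome list in Protocol Section 8.5 has no correct code for a fatal event or for one that resolves with sequelae

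*Protocol*

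**What the plan says.** Section 8.5 sets out what the case report form (CRF) must hold for each adverse event. It introduces the list with "The following details must thereby be entered" and closes by requiring events to be documented on those criteria. The outcome item reads "Outcome (resolved, ongoing, ongoing – improved, ongoing – worsening". The list has no fatal, sequelae, unknown or other option.

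Three other parts of the protocol use outcomes that this list lacks:

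- Section 8.2 defines a serious AE. Its first criterion is that the event "results in deaths", and a later one is "Resulting in persistent or significant disability or incapacity".
- Section 8.3 defines severity. A moderate event is one where "the AE produces no sequelae"; a severe event is one where "the AE produces sequelae, which require prolonged therapeutic intervention".
- Section 7.3.12 describes, as a risk of conversion, "Potential increase of serum creatinine after conversion, which however is anticipated to be reversible".

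For serious events, Section 8.5.1 also requires a written report with at least a "Short description of the event and outcome", and a follow-up report on outcome where applicable. Section 8.5.2 lists death and lasting disability among the items for suspected unexpected serious adverse reactions (SUSARs).

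**The concern.** The protocol itself fixes the outcome list and makes the entry compulsory, so this is not a detail left for a later document. An investigator who follows Section 8.5 cannot truthfully code an event that ended in death, or one that has settled but left a deficit. The same form can then hold a severity grade that rests on sequelae next to an outcome that cannot show them.

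At stake is the accuracy of the coded safety data. Section 10.4.3 says safety will be reported with descriptive statistics, and coded fields are the natural input to such a summary. If lasting damage is entered as *resolved*, the coded outcome looks better than the facts. If a death is entered as a form of *ongoing*, the code is wrong.

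**Working it through.** No arithmetic applies. The check sets the four codes against the outcomes that the protocol itself recognises.

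**1. A fatal event (Section 8.2).** *Resolved* is untrue. The three *ongoing* codes describe an event that continues in a living participant. Matching codes: 0 of 4. The other items listed in Section 8.5 are type, start, end, severity, serious, unexpected and relation to study drug. The serious item is a yes or no and does not ask which criterion was met. Among the listed fields, a death is therefore not distinguished from, say, a hospitalisation, unless the event term happens to say so.

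**2. An event that settles and leaves a deficit (Section 8.3).** *Resolved* hides the deficit, and any form of *ongoing* says the event has not ended. Codes that state recovery with sequelae: 0 of 4. In the Section 8.3 definitions of moderate and severe, the clause on sequelae is the only one not softened by a word such as may or usually. It is the firmest line between the two grades, and the outcome field cannot show it.

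**3. Whether other reports fill the gap.**

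- *Serious and unexpected, suspected drug-related:* the SUSAR report names death and lasting disability, so the outcome is captured there.
- *Serious but expected, or unrelated:* the report under Section 8.5.1 carries the outcome as free text. The information exists but has no category.
- *Non-serious with sequelae:* Section 8.3 states that a severe event need not be serious. Such an event triggers neither report, so the Section 8.5 field is the only outcome entry that the protocol asks for.

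**4. The renal risk in Section 7.3.12.** A creatinine rise that returns to baseline can be coded *resolved*. One that has not recovered can be coded *ongoing* or *ongoing – improved*. Only a rise that stabilises at a permanently worse level has no code of its own. Even then the facts are not lost. The biochemistry table in Section 6 lists creatinine at every visit and at premature end of study, Section 7.4.1.1 requires renal function every four weeks, and the synopsis names glomerular filtration rate as the safety endpoint.

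**The case against.** The best case for leaving the list alone is that nothing important disappears. A death is flagged as serious, reported in writing at once and described with its outcome. Lasting disability is also a seriousness criterion and gets the same report. Graft function is measured numerically against baseline, which is better evidence of reversibility than a code. The severity grade already carries some information on sequelae. The CRF is a separate appendix, not shown, and may offer more options. Within a 12-week treatment period it may also be too early to call a deficit permanent, whatever codes exist.

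Most of this stands, and it limits the point to the coded field. Two parts do not remove it. First, the severity grade is a weak substitute: Section 8.3 itself gives a severe headache and several hours of nausea as examples of severe events, so the grade does not reliably identify sequelae. Second, a fuller CRF would leave Section 8.5 needing alignment with it, because the protocol text is the rule.

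A reader might infer more than the documents support:

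- *That this field is the trial's only record of reversibility.* The repeated creatinine measurements contradict this, and no AE outcome table is specified anywhere.
- *That a creatinine rise is the one named risk.* Section 8.1.1 lists many known and potential risks.
- *That the severity scale depends on death.* Section 8.3 does not define any grade by death; it uses sequelae.
- *That at least 3 of 30 or 5 of 50 patients are affected,* by applying the listed frequency of more than 1 in 10 for creatinine increase. That frequency covers any rise, reversible or not. The protocol gives none for partial permanent loss.

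**Conclusion.** The point holds in a limited form. Section 8.5 makes an outcome entry compulsory and provides no correct code for a fatal event or for one that resolves with sequelae, while Sections 8.2 and 8.3 rely on exactly those outcomes. Every such event would be miscoded or left blank in that field. How many there would be cannot be derived from the protocol.

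The consequence is small. Deaths and serious lasting harm remain visible in the reports for serious events, and renal function remains visible in the laboratory data. The real loss falls on non-serious events with sequelae. The primary analysis and the sample size are unaffected.

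This rests on reading the list in Section 8.5 as complete, which its wording supports but the unseen CRF might qualify.

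**What to change.** In Section 8.5, add three codes to the outcome item: resolved with sequelae (specify), fatal, and unknown. The last is useful because Section 6.1.6 lets a withdrawing participant ask that no further data be recorded, so the final outcome of an open event may never be learned. Make the same change on the AE page of the CRF if the codes are not already there, and check that the wording agrees with the criteria in Section 8.2 and the grades in Section 8.3.

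The cost is one line of protocol text and, at most, one CRF field. It needs no extra patients, visits or procedures.

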### 8. 5. 1 Reporting procedures for SAEs

In the event of serious, the investigator has to use all supportive measures for best patient treatment. A written report is also to be prepared and made available to the clinical investigator immediately.. The following details should at least be available:

- Patient initials and number
- Patient: date of birth, sex, ethical origin
- The suspected investigational medical product (IMP)
- The adverse event assessed as serious
- Short description of the event and outcome
- If applicable, the initial report should be followed by the Follow up report, indicating the outcome of the SAE.

### 8. 5. 2 Reporting procedures for SUSARs

It must be remembered that the regulatory authorities, and in case of SUSARs which could possibly concern the safety of the study participants, also the Institutional Review Board / Independent Ethics Committee (IRB / IEC) are to be informed. Such reports shall be made by the study management and the following details should be at least available:

- Patient initials and number
- Patient: date of birth, sex, ethical origin
- Name of investigator and investigating site
- Period of administration
- The suspected investigational medical product (IMP)
- The adverse event assessed as serious and unexpected, and for which there is a reasonable suspected causal relationship to the IMP
- Concomitant disease and medication
- Short description of the event:
  - Description
  - Onset and if applicable, end
  - Therapeutic intervention
  - Causal relationship
  - Hospitalization of prolongation of hospitalization
  - Death, life-threatening, persistent or significant disability or incapacity

Electronic reporting should be the expected method for reporting of SUSARs to the competent authority. In that case, the format and content as defined by Guidance (28) should be adhered to. The latest version of MedDRA should be applied. Lower level terms (LLT) should be used.

### 8. 5. 3 Annual Safety Report

The Annual Safety Report will be provided by the principal investigator at least once a year.

This report will also be presented annually to the Institutional Review Board / Independent Ethics Committee (IRB / IEC) and to the competent authorities by the sponsor.

# Follow-up

## Follow-up of study participants including follow-up of adverse events

In the present study, study participants will be recruited among the patients who attend the Department of Internal Medicine III, Division of Nephrology and Dialysis, of the Medical University of Vienna for standard care after renal transplantation. All patients undergo regular visits at certain time-intervals, which depend on the time since the transplantation or on the evaluation of the physician (short-term control visit in case of an adverse event, e.g. increase of serum creatinine, infection, or change of immunosuppression). Additionally, patients have the possibility to attend our site in case of an adverse event, e.g. fever, urinary tract infection, diarrhoea, without appointment.

After the end of the study, all study participants will be taken care of in this routine care setting similar to before participation in the study.

## Treatment after end of study

The immunosuppressive regimen after the end of study will depend on the response of HCV-replication on CsA-treatment. Subjects, who have shown a decrease of HCV-RNA of at least log -2, will continue with a CsA-based immunosuppression. Subjects, who did not respond with an attenuation of HCV-replication will be treated with their original tacrolimus-based immunosuppressive treatment-scheme.

# STATISTICAL METHODOLOGY AND ANALYSIS

## Analysis sets

Two different analysis sets are defined:

- **Intention to treat set**

This analysis set includes subjects who received at least one dose study drug,

- **Per-protocol set**

This analysis set comprises all subjects who received study drug (at least one dose) and did not violate the protocol in a way that might affect the evaluation of the effect of the study drug(s) on the primary objective, i.e., without major protocol violations.

## Sample size considerations

A sample size of 26 will have 90% power to detect a difference in means of 1, assuming a standard deviation of differences of 1,5, using a paired t-test with a 0,050 two-sided significance level. Considering a drop-out rate of 10 percent results in a sample size of about 30 patients. If more patients are willing to participate in the study, up to 50 patients will be recruited. In this case more refined mean differences can be detected or a possible higher standard deviation of differences can be accounted for.

Last values will be carried forward (LVCF) in the case of missing values in the outcome variables for the intention to treat analyses. An investigation will be made concerning the sensitivity of the results of analysis to the method of handling missing values, especially if the number of missing values is substantial.

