| STATISTICAL METHODOLOGY | - **Primary Endpoint:** HCV-RNA - **Null and alternative hypotheses:**   **H0** conversion from a tacrolimus- to a cyclosporine A-based immunosuppression has no effects on HCV-replication  **H1**: conversion from a tacrolimus- to a cyclosporine A-based immunosuppression attenuates HCV-replication by one decimal power (one unit of the decadic logarithm) after 12 weeks  **Type-I and -II errors - power.**  α = 5 %  ß = 90 %  .   - **Statistical methodology**   .Paired t-test   - **Sample size calculation.**   A sample size of 26 will have 90% power to detect a difference in means of 1, assuming a standard deviation of differences of 1,5, using a paired t-test with a 0,050 two-sided significance level. Considering a drop-out rate of 10 percent results in a sample size of about 30 patients. If more patients are willing to participate in the study, up to 50 patients will be recruited. In this case more refined mean differences can be detected or a possible higher standard deviation of differences can be accounted for.   - **Main analysis set** - **Other endpoints** | | | | | |
| STUDY EXTENSION | *.* | | | | | |

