## 10. 4 Endpoints analysis

### 10. 4. 1 Primary endpoint analysis

The primary endpoint HCV-RNA will be logarithmically transformed (base 10). The paired t-test used to assess the effect of a conversion from a tacrolimus- to a cyclosporine A-based immunosuppression on HCV-replication after 12 weeks.

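### Carrying the last value forward in the ITT analysis of HCV-RNA biases the week-12 mean change in an unknown direction; the error is modest at 10% drop-out, and a repeated-measures model could use the scheduled week-4 and week-8 data

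*Protocol*

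**What the plan says.** The missing-data rule is in the Protocol under Sample size considerations: "Last values will be carried forward (LVCF) in the case of missing values in the outcome variables for the intention to treat analyses". The next sentence promises to examine how sensitive the results are to the handling of missing values, above all if many are missing. It names no alternative method.

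Section 10.4.1 fixes the test on log10 values: "The paired t-test used to assess the effect of a conversion from a tacrolimus- to a cyclosporine A-based immunosuppression on HCV-replication after 12 weeks".

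Other parts of the Protocol that bear on this:

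- **Analysis sets (10.1).** One dose of study drug is enough for the ITT set; no HCV-RNA value after baseline is required. A per-protocol set is also defined. The Synopsis leaves its entry for the main analysis set empty, so neither set is named as primary.
- **HCV-RNA schedule (section 6 and its table of biochemical measurements).** HCV-RNA is measured at visits 2, 3, 4 and 5, that is at weeks 0, 4, 8 and 12.
- **Stopping for loss of graft function (7.3.12).** After a defined fall in GFR, "the study drug will be discontinued in the respective study participant and immunosuppression re-converted to a tacrolimus-based regimen".
- **Early stopping.** The premature end-of-study laboratory lists (section 6 table and 7.4.1.4) do not include HCV-RNA. The sections on withdrawal and on study drug interruption instead call for the full end-of-study assessments. The first places them 7±3 days after stopping and makes them voluntary. The second places them before stopping, where possible.

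**The concern.** Together, the rule and the test fill in one value per missing patient and then treat it as an observed week-12 result. Depending on when the patient stopped, that value is the baseline itself (change exactly zero), a week-4 value or a week-8 value. A patient re-converted to tacrolimus after week 4 or 8 is scored at week 12 with a value measured on cyclosporine. None of these is the week-12 outcome, either for a patient who stayed on cyclosporine or for one who switched back.

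In a two-arm trial part of such an error may cancel between arms. Here there is one arm and no comparator, so it enters the estimated effect of conversion in full. Stopping is also unlikely to be unrelated to treatment: the Protocol lists raised serum creatinine among the most frequent side effects and ties discontinuation to a fall in GFR. The intermediate HCV-RNA values that would allow a better analysis are already scheduled, but the two-point test uses them only as substitutes for missing week-12 values.

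**Working it through.** **Inputs from the Protocol.** Mean fall 1 log10 at 12 weeks ("attenuates HCV-replication by one decimal power (one unit of the decadic logarithm) after 12 weeks"); SD of differences 1.5 ("assuming a standard deviation of differences of 1,5"); test ("using a paired t-test with a 0,050 two-sided significance level"); drop-out ("Considering a drop-out rate of 10 percent results in a sample size of about 30 patients").

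**The plan's own figure.** The Protocol states: "A sample size of 26 will have 90% power to detect a difference in means of 1". Noncentrality is √26 × 1/1.5 = 3.40 with 25 degrees of freedom, which gives 90.4% power; n = 25 gives 89.2%. Then 26/0.9 = 28.9, so 29, or about 30. The sample size reproduces and is not in question.

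**Assumptions that are not in the Protocol.** A fraction p stops, split equally between before week 4, after week 4 and after week 8, and unrelated to response. Three shapes of mean change at weeks 4, 8 and 12 are used: linear (-1/3, -2/3, -1), plateau (-1, -1, -1) and transient (-1, -0.5, 0). The 30% stopping rate is also an assumption.

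**Bias.** Expected carried-forward mean change = (1-p) × (week-12 change) + (p/3) × (0 + week-4 change + week-8 change).

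- Linear, p = 0.10: 0.90 + 0.0333 × (0 + 0.333 + 0.667) = 0.933. At p = 0.30: 0.70 + 0.10 × 1 = 0.80.
- Plateau, p = 0.10: 0.90 + 0.0333 × 2 = 0.967. At p = 0.30: 0.70 + 0.10 × 2 = 0.90.
- Transient, p = 0.10: 0.0333 × 1.5 = 0.05. At p = 0.30: 0.10 × 1.5 = 0.15.

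| Target at week 12 | p | True fall | Carried forward | Error |
|---|---|---|---|---|
| Had stoppers stayed on cyclosporine | 10% | 1.00 | 0.93-0.97 | 0.03-0.07 too small |
| Had stoppers stayed on cyclosporine | 30% | 1.00 | 0.80-0.90 | 0.10-0.20 too small |
| Stoppers re-converted, back at baseline | 10% | 0.90 | 0.93-0.97 | 0.03-0.07 too large |
| Stoppers re-converted, back at baseline | 30% | 0.70 | 0.80-0.90 | 0.10-0.20 too large |
| Transient response, no effect at week 12 | 10% | 0 | 0.05 | false benefit |
| Transient response, no effect at week 12 | 30% | 0 | 0.15 | false benefit |

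If poor responders are the ones who leave during a gradual decline, simulation (n = 30, 3,000 runs, between-visit correlation 0.7) gives a larger error: a carried-forward mean of 0.89 at 10% drop-out, against a true 1.00, with power 84%.

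**False positives.** In the transient case at 30%, the bias in standard errors is 0.15/0.261 = 0.57. A noncentral t with 29 degrees of freedom then rejects in 8.6% of trials; simulation gave 8.5%. At 10%, 0.05/0.27 = 0.19, which gives 5.4%; simulation gave 5.2%. With no change at any visit and random stopping, rejection stays at about 4-5%.

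**Standard error.** Take the extreme in which every stopper carries baseline. The variance is (1-p) × 2.25 + p(1-p) × 1.

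- p = 0.10: 2.025 + 0.09 = 2.115, SD 1.454, SE 1.454/√30 = 0.266. The 27 completers give 1.5/√27 = 0.289.
- p = 0.20: 1.80 + 0.16 = 1.96, SD 1.40, SE 0.256. The 24 completers give 0.306.

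In simulation with random stopping and a linear fall, the t-test SE agreed with the actual sampling SD of the carried-forward mean: 0.270 and 0.270 at 10%, 0.263 and 0.265 at 30%. The repeated-measures estimate of the week-12 mean had sampling SD 0.285 and 0.317 in the same cases, with means of 1.01 and 0.99 against a true 1.00.

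**The case against.** Four objections carry weight.

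**The effect is small at the planned drop-out.** At 10% the error is 0.03-0.07 log10 when stopping is unrelated to response, against a target of 1 and an SE of about 0.27, and power stays above 90%. This stands. The larger figures need 30% stopping, which the Protocol does not predict.

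**A reader might infer that the filled-in SD is too small and the t-test therefore invalid.** The numbers do not support that. The SE is right for the quantity the test estimates, and the SD of the filled-in data is not always below 1.5; it was 1.53-1.57 when poor responders left during a gradual decline. What holds is narrower: the SE is too small as a measure of uncertainty about the week-12 mean. A reader might also infer inflated false positives in general. They arise materially only with a transient response and heavy drop-out.

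**The mixed model does not recover the outcome of re-converted patients.** Without values after stopping it estimates 1.00 where the true mean with re-conversion is 0.70, an error of 0.30, more than that of carrying forward. This stands as a limit: under missing at random the model answers what would have happened had patients stayed on cyclosporine. Nor can one assume that post-stopping values will be available at no cost, because the Protocol does not secure them.

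**A sensitivity investigation and a per-protocol set are already planned.** This softens the point. But carrying forward remains the stated rule for the ITT analyses, and no alternative is named.

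It would also be too strong to call this a fault of the primary analysis. The Protocol names neither set as primary, so the point concerns the ITT analysis of the primary endpoint.

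**Conclusion.** The point holds in this limited form. The ITT analysis of the primary endpoint rests on a fill-in rule that misstates the week-12 mean change. The sign of the error depends on the unknown trajectory and on what happens to patients after stopping. If stopping is unrelated to response, the error is about 0.03-0.07 log10 at the planned 10% and 0.10-0.20 at an assumed 30%; at 10% it reaches about 0.11 if poor responders leave during a gradual decline. A transient response with 30% stopping would raise false positives to roughly 8-9%. All these sizes rest on assumed trajectories and stopping patterns and on n = 30; none is a Protocol figure. A better method is available from data already scheduled, so the change is worth making, but the defect would not by itself overturn the trial's result at the planned drop-out.

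**What to change.** Replace the rule for the ITT analysis of HCV-RNA with a likelihood-based repeated-measures mixed model:

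- log10 HCV-RNA at visits 2-5, visit as fixed effect, unstructured within-patient covariance;
- contrast week 12 minus visit 2, with 95% CI. With complete data this reproduces the paired t-test.

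State that under missing at random this estimates the effect had patients stayed on cyclosporine. Name the sensitivity analyses: last value carried forward, completers' paired t-test, and an analysis that returns re-converted patients to baseline. Say which analysis set is the main one.

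Reconcile the premature end-of-study laboratory lists (section 6 table, 7.4.1.4) with the sections on withdrawal and on study drug interruption, so that it is clear whether and when HCV-RNA is measured at early stopping. Values after stopping can be used as observed only if they are collected.

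Cost: Protocol wording and a short program in SAS, which is already listed among the software. No extra patients are needed. Extra samples arise only if the reconciliation adds HCV-RNA at early stopping. The downsides are reliance on missing at random, a slightly wider interval than with carried-forward values, and little gain for patients who leave before week 4.
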